#### PA club evaluation

PA club instructors use the Internet-based program to record reach (e.g., girl’s attendance and punctuality at PA club). To assist the researchers in evaluating dose, one of the PA club staff members serving as the club manager records the types of activities offered for the day, including whether healthy snacks were distributed.

The second author trained four process evaluators to evaluate the PA club via an observation tool and a quantitative checklist with rating scale in the first mo. (week 3), at the midpoint (week 9), and near the end (week 15). The checklist includes items for evaluating dose delivered or staff adherence to specific areas associated with the PA club protocol and fidelity or the degree that the PA club reflects important theoretical concepts of the HPM (e.g., enjoyment - “fun” PAs offered) and SDT (e.g., autonomy, relatedness, competence). A process evaluator evaluates the entire session for one day during one week, and another process evaluator evaluates the session on another day during the same week. They report to the second author at the end of each week and discuss their findings. The second author or intervention coordinator intervenes as needed with the PA club instructors to promote interventionist consistency in adhering to the protocol.

Five girls per school are randomly selected every other week to wear the ActiGraph GT3X-plus to measure the girls’ level of PA during the club time. To determine dose received, data are downloaded at the end of each week to a computer. A research team member (e.g., intervention coordinator, project manager, principal investigator, co-investigator) randomly monitors a session at each club at least weekly to evaluate adherence to protocols and retrain staff as needed. During the middle of the first half of the intervention, the manager contacts parents/guardians of all girls who missed a week (all 3 days) or more than an average of two PA club sessions in a week over the initial three 3-week period to explore ways to help the girls attend the club and attain adequate PA.

#### Nurse counseling evaluation

To assist the research team in evaluating reach and dose, the nurse uses the Internet-based program to record each girl’s attendance at and date of the counseling session, plus the start and end time of the session. For girls who miss a week (all 3 days) or more than an average of two PA club sessions in a week, the nurse records reasons for not attending the PA club after each girl’s counseling session. All sessions for assented participants who have written parental/guardian permission are audio-taped with a portable digital recorder. In the pilot, we found that giving the nurse a recorder to tape sessions was more efficient than randomly selecting a few sessions for audio-taping and having research assistants traveling to the school to record them. Also, this approach ensures that all sessions are being delivered as planned. The nurse will allow each participant to consent or refuse to be audio-taped at the beginning of each session. After the nurse conducts approximately 6 sessions, the first author meets with the nurse to evaluate one of the audio-taped sessions together (in collaboration) with the nurse and reinforce motivational interviewing principles.

To further determine adherence to the counseling protocol and motivational interviewing principles, our statistician randomly selects two audiotapes from those recorded by each nurse in the first session to be transcribed verbatim. Following evaluation of the transcripts and prior to the second session, the first author meets and discusses the two selected cases with the respective nurse on an individual basis to assist the nurse in adhering to the technique to avoid drift and ensure interventionists’ consistency, troubleshoot, and offer strategies for enhancing motivational interviewing skill transfer during the final session. During the middle of the second half of the intervention, the nurse contacts all parents/guardians to encourage them and explore ways to help their daughter continue her physical activity after the club ends.

The first and third author will evaluate the two audio-recordings and transcripts from the first session and two from the second session at each of the four intervention schools per year. Similar to the pilot study, the Motivational Interviewing Treatment Integrity (MITI) Code will be employed [63]. Both authors have expertise in using the MITI, a reliable, valid, and sensitive scale for evaluating motivational interviewing fidelity [63,64].

### Evaluation of intervention components - immediately post-intervention

Girls in the intervention group will evaluate each intervention component (nurse counseling, Internet-based program, and the PA club) by responding to the Girls on the Move Intervention Evaluation Instrument (developed for the pilot study) that will be integrated into the Internet-based program. The nurse and PA club instructors will complete a self-evaluation form that will be compared with the girl’s evaluations. Descriptive statistics will be obtained. Matched pairs t-tests will be used to compare the data. A research team member will share evaluative findings with the nurse and PA club instructors in individual interviews at their respective schools; and ask the nurse and PA club instructors about satisfaction with intervention, its feasibility, problems meeting objectives, and recommendations for improvement; and record comments.

### Sample size determination and data analysis

#### Power calculations

Sample size calculations incorporated school-based research power approaches [65,66] and were informed by the work done in our pilot study and other studies using MVPA as a primary outcome [67,68]. We assumed a small effect size of 0.20 and an intraclass correlation coefficient (ICC) of 0.02, as noted from the Trial for Activity in Adolescent Girls [67]. Assuming a standard deviation of 80 for minutes of MVPA over 7 days [68], this effect size of 0.20 corresponds to a difference of 16 minutes/week between groups. Given that girls receiving the intervention are encouraged to accumulate at least 60 minutes/day of MVPA, this mean difference is reasonable to expect with a control group that consists of a number of girls who may have never been involved in any organized MVPA due to obstacles, such as limited free or low-cost programs [69]. Using this effect size and ICC, 24 schools (12 intervention) with 50 girls per school would provide power .80 and alpha = 0.05 for two-tailed comparison between two groups. To allow for 20% attrition (12 girls per school) [36,69-71], we plan to recruit 62 girls per school each year.

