### Aims and hypotheses

The main study aim is to evaluate the efficacy of our comprehensive 17-week school-based intervention in increasing girls’ minutes of MVPA and improving CV fitness, BMI, and percent body fat immediately post-intervention (after 17 weeks) and at 9-month post-intervention follow-up (F/U; 9 months after end of intervention). The primary outcome is minutes of MVPA measured after 17 weeks. The intervention includes three components, two of which are individual-level: 1) two face-to-face motivational, individually tailored counseling sessions with a registered nurse, and 2) an interactive Internet-based session during which each girl receives individually tailored motivational and feedback messages (11 weeks). One group-level component, a PA club led by PA instructors (e.g., individuals from community who have experience conducting youth physical activity programs; teachers, including physical education; and sports team coaches), provides an important venue after school to assist girls in establishing a behavioral pattern of MVPA. Girls receiving the intervention will be compared to those in control schools having usual school offerings, some of which may include physical education.

Specific hypotheses include:

•Immediately post-intervention, minutes of MVPA (measured by accelerometer) will be greater by 16 minutes/week among girls in intervention, as compared to control, schools.

•At 9-month post-intervention F/U, minutes of MVPA will be greater among girls in the intervention than control schools.

•Immediately post-intervention and at 9-month post-intervention F/U, CV fitness will be higher and BMI and percent body fat will be significantly lower among girls in the intervention than control schools.

A secondary objective is to examine if MVPA changes are mediated by cognitive (e.g., perceived benefits of PA, barriers to PA, PA self-efficacy, social support) and affective variables (e.g., enjoyment of and motivation for PA).

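### The stated power of .80 does not follow from the stated inputs: effect size 0.20, ICC 0.02 and 24 schools of 50 girls give two-sided power of about .65 to .69

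*Protocol article*

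**What the plan says.** The Power calculations section gives every input for a two-arm comparison of means with schools as clusters. On effect and clustering it says: "We assumed a small effect size of 0.20 and an intraclass correlation coefficient (ICC) of 0.02". The scale is set by "Assuming a standard deviation of 80 for minutes of MVPA over 7 days", from which "this effect size of 0.20 corresponds to a difference of 16 minutes/week between groups". The section then attributes the result to that effect size and that ICC: "24 schools (12 intervention) with 50 girls per school would provide power .80 and alpha = 0.05 for two-tailed comparison between two groups". Recruitment of 62 girls per school is described as an allowance for 20% attrition, so 50 is the number expected to be analysed.

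The same 16 minutes appears as the first hypothesis under Aims and hypotheses: "minutes of MVPA (measured by accelerometer) will be greater by 16 minutes/week among girls in intervention". That section names MVPA after 17 weeks as the primary outcome, so this is the power statement for the primary comparison.

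Two other features bear on precision but are not inputs to the calculation. Study design pairs schools before randomization. Data analysis and Primary analyses plan a multilevel model with the baseline value of the outcome as a covariate (Statistical Model #1). The Power calculations section gives no baseline to follow-up correlation, variance reduction or gain from pairing.

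**The concern.** Because all the inputs are printed, the figure can be checked from the document alone, and it fails by 11 to 15 percentage points. That is too much for rounding or for the choice between a normal and a t reference distribution.

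The figure is the justification for the size of the trial. If the 17-week comparison is null, readers will take it as coming from a trial with a 20% chance of missing a true difference of 16 minutes per week. On the printed inputs, an unadjusted comparison would miss that difference 31% to 35% of the time, about one time in three. The null result would then be read as stronger evidence against the intervention than the stated design supports.

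**Working it through.** **Inputs (all from Power calculations).** Effect d = 16/80 = 0.20; ICC ρ = 0.02; k = 12 schools per arm; m = 50 girls per school; alpha 0.05, two-tailed.

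**Standard error.**
- Design effect = 1 + (m − 1)ρ = 1 + 49 × 0.02 = 1.98.
- Effective number per arm = 600/1.98 = 303.
- Variance of the standardised difference = (2/k) × [ρ + (1 − ρ)/m] = (2/12) × (0.02 + 0.98/50) = 0.0066.
- SE = √0.0066 = 0.0812, and d/SE = 0.20/0.0812 = 2.46.

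**Attempt to reproduce .80.**

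| Calculation | Normal | t, 22 df |
|---|---|---|
| As stated: two-sided, 50 per school | .692 | .653 |
| Two-sided, 62 per school (no attrition) | .735 | .697 |
| One-sided 5%, 50 per school | .793 | .770 |
| Two-sided, ICC changed to 0.01 | .810 | .774 |

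The 22 degrees of freedom are 24 schools minus 2. Treating the design as 12 matched pairs (11 df), with no gain in precision from matching, gives .612. Ignoring clustering gives .934.

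Of the variants that keep the stated effect, ICC and 50 girls in each of 24 schools, and add no unstated input, only the one-sided 5% test comes near .80. That conflicts with the section's own wording, "power .80 and alpha = 0.05 for two-tailed comparison between two groups". It is a possible origin of the figure, but the document does not confirm it.

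**What the stated design can detect.** Solving for d at 80% power with 12 schools per arm gives 0.228 (normal) or 0.238 (t). Multiplied by 80, these are 18.2 and 19.1 minutes per week.

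**What .80 would require without covariates.** At d = 0.20, ICC 0.02 and 50 per school, 16 schools per arm give .811 (normal) and 17 per arm give .811 (t, 32 df).

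**What .80 would require from baseline adjustment.** Assume that the baseline value, with correlation r at both levels, multiplies both the school and the girl variance by (1 − r²). Then SE = 0.0812 × √(1 − r²). The document gives no r, so a range is shown. One degree of freedom is taken for the covariate (21 df).

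| r | Normal | t, 21 df |
|---|---|---|
| 0.3 | .73 | .69 |
| 0.4 | .77 | .73 |
| 0.5 | .81 | .77 |
| 0.55 | .84 | .80 |
| 0.6 | .87 | .83 |

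Power reaches .80 at r = 0.48 (r² = 0.23) by the normal approximation and at r = 0.55 (r² = 0.30) by the t test.

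**The case against.** The best defence is that .65 to .69 describes an unadjusted comparison, which is not the planned test. Statistical Model #1 conditions on the baseline outcome, and a correlation of 0.5 to 0.6 would bring power to between .77 and .87. Pairing of schools might also help. The section cites school-based power methods and a pilot study, and a journal article condenses its protocol, so a covariate or matching term may have been used and left out here. The one-sided explanation is conjecture, since an ICC of 0.01 would also give about .80. Finally, the analysis does not use the power figure, and effect sizes with confidence intervals are promised, which limits the misreading of a null result.

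Much of this stands as a limit on the conclusion. The one-in-three miss rate applies to the unadjusted comparison only, the adjusted analysis may well have adequate power, and the origin of .80 is unknown. It does not rescue the sentence. The section attributes .80 to the effect size and ICC that it prints and names no other input. Leaving out detail is normal in an article, but a printed result that disagrees with its printed inputs is an error. If a baseline correlation lies behind .80, the text credits the result to the wrong assumptions and the reader cannot judge whether that correlation is plausible. Pairing without a stated gain does not help either: on 11 df it lowers power to .61.

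**Conclusion.** The concern holds. On the protocol's own inputs, two-sided power is .69 (normal) or .65 (t, 22 df) against a stated .80, and the difference detectable with 80% power is 18 to 19 minutes per week rather than 16. These figures assume equal school sizes of 50, no covariate gain and no matching gain, which is the calculation as described. Whether the baseline-adjusted primary analysis reaches .80 depends on an unstated correlation. It does so only if r is about 0.48 to 0.55 or higher at both school and girl level. Because this is the size justification for the primary outcome, it must be corrected.

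**What to change.** Choose one of two corrections to the Power calculations section.

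1. **Preferred, because it matches the planned test.** Compute power for Statistical Model #1. State the assumed correlation between baseline and 17-week MVPA and its source, say whether it applies at school level, girl level or both, name the reference distribution and degrees of freedom, and show power for r from 0.3 to 0.6. About 0.55 is needed for .80 on the t distribution.
2. **Otherwise, restate the figure and label it unadjusted.** Suggested wording: *Without covariate adjustment, 24 schools with 50 girls each give two-sided power of about .65 (t, 22 df; .69 by normal approximation) for 16 minutes per week; the difference detectable with 80% power is about 19 minutes per week (18 by normal approximation).*

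If the original calculation was one-sided, or used a smaller or covariate-adjusted ICC, say so and reconcile it with the two-tailed test and the ICC of 0.02 now printed.

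The cost is one paragraph. The sample, the test and the alpha level stay as they are. The stated power either becomes less favourable or rests on an assumption that readers can check.

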#### Data analysis

Data will be analyzed using SAS 9.3 (SAS Institute Inc., Cary, NC) [72]. Outcome measures include the primary outcome: minutes of MVPA; secondary outcomes: CV fitness, BMI, and percent body fat; and mediating cognitive and affective variables. Potential covariates measured at baseline are personal factors and behaviors. To adjust for non-independence of observations within each school and the dependence within person, analyses below will be carried out using a multilevel model approach frequently used in group randomized trials [73] that will incorporate baseline measures as covariates [74,75]. Multilevel generalized linear models [73,76] will be fit for ordinal, and discrete outcomes using appropriate link functions. Assumptions of normality for continuous outcome variables will be evaluated; normalizing transformations or generalized linear mixed effect models will be used if warranted [76].

#### Preliminary analyses

Descriptive statistics, such as means and proportions, will be provided for outcomes and baseline measures. Pattern of missing data will be evaluated and missing at random mechanism will be assumed [77]. We will collect information on participants who dropped out and baseline characteristics of those who dropped out will be compared by group to provide information of any potential attrition bias.

#### Primary analyses

Primary analysis is of intention to treat type [78,79], which gives a conservative estimate of treatment effect compared with what would be expected if there was full compliance [80]. Effect sizes and their confidence intervals (adjusted for baseline values of outcomes and nested study design) will be computed. Variance components (school and participants) will be estimated.

We will use: Statistical Model #1: Outcome (after 17 weeks) = outcome (baseline) + study group + covariates. The essential parameter tested in this model is the coefficient for the study group variable. Covariates will be included if preliminary analyses reveal group differences at baseline despite randomization. We will model 9-month post-intervention F/U MVPA, controlling for MVPA after 17 weeks (immediately post-intervention): MVPA (9-month post-intervention F/U) = MVPA (after 17 weeks) + study group + covariates.

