Although different epoch levels can be selected, initial analysis will be conducted using count cut-points (15-second epochs) created by Evenson and colleagues [40]. Prior research by one of the study authors showed these cut-points have the best sensitivity and specificity when compared to others [41]. Count thresholds will be used for activity intensities: moderate (574–1002 counts/15 seconds) and vigorous PA (≥1003 counts/15 seconds). Fifteen-second increments with counts at or above 574 will be summed from 6 A.M. to midnight to determine minutes of MVPA. Data will be excluded if the monitor is taken off during waking hours (noted by 20 or more consecutive minutes of continuous zeros - not observed in an awake child wearing an accelerometer) [42]. Guided by the 80% rule, we plan to use data on participants who provide at least 4 days of data (a significant increase in reliability occurs at 4 days). On weekdays and weekends, we expect monitors to be worn 11.2 hours and 7.2 hours, respectively (adolescents are expected to be awake 14 hours/day on weekdays and 9 hours/day on weekends so 80% corresponds to 11.2 and 7.2 on weekdays and weekends, respectively) [43].

Cardiovascular fitness is determined using the Progressive Aerobic CV Endurance Run (PACER) [44], a 15-meter or 20-meter shuttle run, that estimates aerobic capacity and CV endurance. No more than six participants at a time run from one line to another on a flat surface, according to audio cues. Each time participants complete a run in one direction, it is considered completion of one lap. The distance (15 versus 20 meters) of one lap is determined by space available. The pace of the audio cues increases with time until participants can no longer complete the laps in the time allotted. Staff members record number of laps completed for use in analysis (higher number of laps = greater CV fitness) [44]. Students are considered finished with the test when they have not completed two laps within the allotted time. Number of laps completed is converted to estimated VO_2_ for analysis. PACER has been used with overweight adolescent girls [45]. It avoids singling out lesser fit individuals by allowing them to finish first rather than last with everyone watching.

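### Fitted as written, Model #1 with the 4-day wear rule leaves out enrolled girls without valid MVPA at baseline or at 17 weeks, although the analysis is labelled intention to treat

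*Protocol article*

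**What the plan says.** Four statements in the protocol article bear on who is analysed for the primary outcome, MVPA at 17 weeks.

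- **Label** (Primary analyses): "Primary analysis is of intention to treat type", explained as a choice "which gives a conservative estimate of treatment effect compared with what would be expected if there was full compliance".
- **Model** (Primary analyses): "Statistical Model #1: Outcome (after 17 weeks) = outcome (baseline) + study group + covariates". Covariates enter if the arms differ at baseline. The 9-month MVPA value is the response in a separate model that conditions on the 17-week value.
- **Wear rule** (Measures, Outcomes): "Guided by the 80% rule, we plan to use data on participants who provide at least 4 days of data".
- **Missing data** (Preliminary analyses): "Pattern of missing data will be evaluated and missing at random mechanism will be assumed", and "baseline characteristics of those who dropped out will be compared by group to provide information of any potential attrition bias".

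The Power calculations section counts 50 girls per school out of 62 recruited, allowing for 20% attrition. The Study design section provides for a monitor to be worn for a second week when wear time was inadequate.

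**The concern.** An intention-to-treat label leads a reader to expect every enrolled girl to be accounted for in the arm of her school. The model and the wear rule do not deliver that by themselves. A girl with no valid 17-week value has no response. A girl with a valid 17-week value but no valid baseline has a missing covariate and is dropped as well.

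Assuming missing at random does not bring these girls back. A likelihood mixed model makes use of an incomplete record only when the girl's other measurements are also responses. Here baseline is a covariate and the 9-month value sits in another model. The Data analysis section refers to dependence within person, but each model written out has one response per girl.

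At stake is the primary estimate. Families learn the school's allocation after baseline and before the 17-week measurement, and only intervention schools have the club, the nurse sessions and the related calls to parents. Drop-out or non-wear could therefore differ by arm and relate to activity.

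**Working it through.** **1. The plan's own counts.** Recruited: 24 × 62 = 1,488. Counted in the sample size: 24 × 50 = 1,200. Difference: 288 girls, 288/1,488 = 19.4%, consistent with the stated 20% (50/0.80 = 62.5). The sample size thus already expects about a fifth of enrolled girls not to contribute.

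**2. Who drops out of Model #1 as written.**

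| Valid baseline | Valid 17 weeks | Used by Model #1 | Other data that may exist |
|---|---|---|---|
| yes | yes | yes | – |
| no | yes | no | 17-week outcome, questionnaires, 9-month MVPA |
| yes | no | no | baseline MVPA, short wear, 9-month MVPA |
| no | no | no | questionnaires, short wear, 9-month MVPA |

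The second row is the clearest loss, because the primary outcome itself was observed.

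**3. Size of that loss.** The article gives no rate of valid wear, so the share is assumed. Start from the plan's 50 per school and let a share of them lack a valid baseline. Power by the normal approximation is Φ(0.20/√(2·DE/(12m)) − 1.96), with DE = 1 + (m − 1) × 0.02 and m girls analysed per school.

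| Share lacking baseline | m | Unused 17-week outcomes | DE | Power |
|---|---|---|---|---|
| 0% | 50 | 0 | 1.98 | 0.692 |
| 10% | 45 | 24 × 5 = 120 | 1.88 | 0.669 |
| 20% | 40 | 24 × 10 = 240 | 1.78 | 0.641 |

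The first row does not reproduce the stated power of 0.80. That is a separate matter: 0.80 would need baseline adjustment to remove roughly 20–30% of the variance (power 0.786 to 0.837). What matters here is the difference between rows. If the allowance of 12 girls per school already covers invalid wear, there is no loss beyond the first row.

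**4. Possible bias.** In each arm, the analysed mean exceeds the mean of all enrolled girls by (share missing) × (gap between analysed and missing girls). The bias in the contrast is the difference in shares × gap × SD, with the article's SD of 80 min/week. Shares and gaps are assumed, and the gap is what remains after the model's adjustment.

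- 25% v 20% missing, gap 0.3 SD: 0.05 × 0.3 × 80 = 1.2 min/week
- 25% v 15%, gap 0.3 SD: 0.10 × 0.3 × 80 = 2.4 min/week, which is 15% of the 16-minute target
- 30% v 15%, gap 0.4 SD: 0.15 × 0.4 × 80 = 4.8 min/week

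These figures show what unexplained differential loss could do. They do not measure what a better analysis recovers: imputation or a joint model removes only the part of the gap that 9-month MVPA, wear time or other recorded data explain.

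**The case against.** The strongest reply is that the article nowhere says complete-case. A one-line equation does not define an analysis set, and a missing-at-random assumption is compatible with imputation before Model #1. An analysis plan that is not shown may specify it. That stands. A reader might infer that the protocol plans to restrict the analysis to girls valid at both waves; the text does not say so, and the exclusion is only what follows from the stated rule and equation with nothing added.

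Other parts of the reply also stand:

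- A reader might say that randomised girls are dropped. Schools are randomised, so the accurate term is enrolled girls in randomised schools.
- A reader might take the article to claim a conservative estimate in the face of missing data. Its wording compares only with full compliance, and analysing girls by their school's arm whatever their attendance fits that meaning.
- A reader might assume that the 4-day rule removes girls beyond the 20% allowance. No validity rate is given, and re-wear and the reminder calls reduce the loss, although they cannot help girls who leave or still fall short.
- If outcomes are missing at random given baseline MVPA, arm and the covariates used, Model #1 on the observed outcomes is valid, and imputing from the same variables adds almost nothing. Baseline-adjusted multilevel regression is a standard primary analysis for this design.

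What the reply does not remove is the mismatch among the things the article did choose to fix. The label, wear rule and equation agree only if a further step is added, and none is mentioned. The covariate rule also admits variables because the arms differ at baseline, not because they predict drop-out, so the comparison of girls who dropped out has no stated route into the model.

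**Conclusion.** The point holds in a limited form. Run as written, the primary model excludes enrolled girls without valid accelerometry at baseline or at 17 weeks, so the intention-to-treat label is not met in the sense of including all enrolled girls. The missing-at-random assumption is carried by fewer variables than the trial collects.

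The consequence is probably modest. Girls lacking only a baseline value are lost needlessly: 120 to 240 of them under the assumed 10–20%, for a power loss of about 0.02 to 0.05. Bias arises only if loss differs by arm and still relates to activity after adjustment. The 1.2–4.8 min/week range is hypothetical. The documents support neither the conclusion that the primary estimate is biased nor the conclusion that Model #1 is the wrong model.

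**What to change.** Keep Model #1 as the primary model and state the analysis set as all enrolled girls in the randomised schools. Before fitting it, carry out multilevel multiple imputation by arm, respecting school, with MVPA at baseline, 17 weeks and 9 months, wear time and predictors of drop-out in the imputation model. A joint longitudinal mixed model serves the same purpose: all three waves as responses, baseline mean constrained equal across arms, school effects, and the 17-week contrast as primary. It uses the other auxiliary variables only if they are added. Report the complete-case fit of Model #1 as a sensitivity analysis.

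If neither is adopted, describe the primary analysis as available-case under missing at random.

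The cost is plan wording and a little more programming, with no new data or participants. The benefit is that girls missing only baseline are kept, and bias is reduced where the auxiliary data explain the missingness.
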